## Abstract

**Background:**

Apnoea of prematurity (AOP) is one of the most common diagnoses among preterm infants. AOP often leads to hypoxemia and bradycardia which are associated with an increased risk of death or disability. In addition to caffeine therapy and non-invasive respiratory support, doxapram might be used to reduce hypoxemic episodes and the need for invasive mechanical ventilation in preterm infants, thereby possibly improving their long-term outcome. However, high-quality trials on doxapram are lacking. The DOXA-trial therefore aims to investigate the safety and efficacy of doxapram compared to placebo in reducing the composite outcome of death or severe disability at 18 to 24 months corrected age.

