## Background

Apnoea of prematurity (AOP), a cessation of breathing, is one of the most common symptoms of an immature breathing system and affects almost 80% of the preterm infants born below a gestational age (GA) of 28 weeks [1]. This poor respiratory control leads to episodes of intermittent hypoxemia and bradycardia. Hypoxemic episodes, especially if prolonged, are associated with increased risks for late death or disability, including motor impairment, cognitive or language delay and risk for visual impairment [2, 3].

Non-invasive respiratory support and caffeine therapy are typically administered to prevent intermittent hypoxemia in preterm infants [4]. Endotracheal intubation and invasive mechanical ventilation can resolve persisting AOP by decreasing the frequency and intensity of hypoxemic episodes, but are associated with an increased risk for bronchopulmonary dysplasia (BPD) and neurodevelopmental impairment [5, 6]. The use of invasive mechanical ventilation is therefore restricted as much as possible in preterm infants. Until now, no consensus has been reached on the optimal treatment strategy for AOP because high-quality trials are lacking.

Doxapram, a respiratory stimulatory analeptic drug, might be considered as an add-on treatment to non-invasive respiratory support and caffeine treatment for persisting AOP in preterm infants. It stimulates the respiratory drive through the brainstem respiratory centre, and the peripheral carotid and aortic chemoreceptors [7]. Unfortunately, well-designed and adequately powered trials on the clinical effect of doxapram are missing. Several observational studies found that treatment with doxapram can be beneficial in reducing the apnoea rate and the number of hypoxemic episodes [8–10]. Doxapram therapy may also be effective in preventing preterm infants from invasive mechanical ventilation [11]. Doxapram may potentially improve neonatal outcomes by preventing preterm infants from the risks, including development of BPD, associated with hypoxemic episodes and invasive ventilation.

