## Methods and analysis

### Trial design

The DOXA-Trial is a multicentre, double blinded, randomized, placebo-controlled trial with two arms, designed to evaluate the superiority of doxapram compared with placebo in the treatment of AOP. This study protocol followed the SPIRIT (Standard Protocol Items: Recommendations for Interventional Trials) guidelines [22], whereas the trial will adhere to the CONSORT (Consolidated Standards of Reporting Trials) statement [23].

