	**Complications:** - Incidence of late-onset sepsis - Meningitis after inclusion - Need for inotropes/ respiratory support	Logistic regression analysis will be performed for all complications, corrected for GA and centre.	Hospital discharge
	- Retinopathy of prematurity	Logistic regression analysis, corrected for GA and centre, will be performed for retinopathy ‘yes’ or ‘no’.	Hospital discharge
	- Hearing loss	Logistic regression analysis, corrected for GA and centre, will be performed for hearing loss ‘yes’ or ‘no’.	Hospital discharge
**Long-term outcomes**	- Readmission since first hospital discharge - Body weight - Body length - Head circumference - Behavioural problems (Child Behavior Checklist) - Cognitive and language development	Logistic regression analysis will be performed for readmissions, behavioural problems, and cognitive and language problems. Linear regression analysis will be performed for body weight, body length, and head circumference. In both analysis will be corrected for GA and centre. Survival analysis will be performed for the time to readmission.	Eighteen to 24 months of corrected age
**Cost-effectiveness**	- (Non-)medical costs during and after hospital admission - Patient outcomes; survival, severe disability, and health-related quality of life (HRQoL)	The total costs per patient and quality-adjusted life years (QALYs) will be assessed. Incremental cost-effectiveness ratios (ICERs) will be calculated, expressed as incremental costs per additional survivor without severe disability at 2 years and incremental costs per QALY gained.	Eighteen to 24 months of corrected age
**Pharmacokinetics**	- Blood samples	Exposure of (keto-) doxapram will be calculated from an existing PK model. The cumulative exposures will be calculated and analysed using a linear regression model, corrected for centre.	During level 3 NICU admission
**Respiratory effects**	- Vital sign data (oxygen saturation, respiratory rate, heart rate, blood pressure) - Ventilation data (ventilation mode, fraction of inspired oxygen, flow)	Vital sign data will be analysed as continuous data. Logistic regression analysis will be performed for all vital sign data, corrected for GA en centre. Mixed model analysis will be performed to take into account repeated measurements. Ventilation duration and cumulative inspired oxygen need and flow will compared using the *t*-test or Mann-Whitney test.	During level 3 NICU admission

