### Vital sign data analyses

Some of the participating centres will collect continuous high frequency monitor data that will be used to analyse the oxygenation in infants receiving either placebo or doxapram. Data on oxygen saturation (SpO_2_), heart rate and respiratory rate will be extracted from bedside monitors where possible. These measurements are part of the standard of care and will be performed without additional burden for participating infants. The vital sign data will be used to investigate the response to doxapram therapy compared to placebo, to identify responders and non-responders to doxapram therapy, and to explore the possibilities of real-time therapy evaluation.

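### The respiratory-effects row of Table 1 names no episode-based measure and gives conflicting analysis types, although fewer apnoeas and hypoxaemic episodes is the drug's stated direct effect

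*Protocol article*

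**What the plan says.** The rationale is about episodes. The Abstract says "doxapram might be used to reduce hypoxemic episodes and the need for invasive mechanical ventilation in preterm infants". The Background adds that "treatment with doxapram can be beneficial in reducing the apnoea rate and the number of hypoxemic episodes", according to observational studies, and that "Hypoxemic episodes, especially if prolonged, are associated with increased risks for late death or disability". Trial design describes a trial "designed to evaluate the superiority of doxapram compared with placebo in the treatment of AOP".

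In Table 1 (Secondary outcomes), the row on respiratory effects lists "Vital sign data (oxygen saturation, respiratory rate, heart rate, blood pressure" and, separately, ventilation settings. For the vital signs it gives three instructions in sequence:

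- "Vital sign data will be analysed as continuous data"
- "Logistic regression analysis will be performed for all vital sign data, corrected for GA en centre"
- a mixed model to allow for repeated measurements.

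The sub-study section Vital sign data analyses says that some centres will collect "continuous high frequency monitor data that will be used to analyse the oxygenation in infants receiving either placebo or doxapram". It also intends to study response against placebo and to separate responders from non-responders. It defines neither an episode nor a response.

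**The concern.** Apnoea, desaturation and bradycardia are short events. An infant can have many of them and still have an hourly mean saturation close to that of an infant with few. The level is also supported by supplemental oxygen, which the same Table 1 row records. A comparison of levels is therefore a weak test of whether the drug reduces episodes.

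The logistic-regression sentence does not fill the gap, because it names no event to model.

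At stake is the reading of the monitor data. A null result on saturation level could be reported as no effect on oxygenation when episodes had in fact fallen substantially.

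**Working it through.** **1. Search of the listed outcomes for an episode measure.**

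| Place in the protocol article | Episode count, rate, duration or time below a threshold? |
|---|---|
| Primary outcome | No: death or severe disability |
| Table 1, respiration | No: intubation, days of support and oxygen, complications, steroids; time to intubation is analysed |
| Table 1, respiratory effects | No: four raw signals and ventilation settings |
| Secondary short-term and long-term outcomes | No |
| Adverse drug reactions | Tachycardia and hypertension, but not apnoea, bradycardia or desaturation |
| Sub-studies (vital signs, neuromonitoring, pharmacokinetics) | None named |

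**2. Internal consistency of the respiratory-effects row.** Logistic regression needs a binary outcome. The row calls the data continuous and defines no cut-off. The two sentences cannot both apply to the same variable. Followed literally, the row gives an analysis of continuous signals or a binary model without an outcome. Neither is an episode analysis.

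**3. How insensitive could a level be? Illustration only.** The documents give no episode rate, depth, duration or standard deviation, so there is no plan figure to reproduce and every input here is assumed.

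Central case: median 6 episodes per hour, 30 s each, 15 saturation points deep; SD of log rate 0.8; between-infant SD of mean saturation 2 points; episodes halved.

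- Mean rate = 6 × exp(0.8²/2) = 8.26 per hour.
- Average saturation lost to episodes = 8.26 × 30/3600 × 15 = 1.03 points. Halving recovers 0.52 points.
- SD including the episode-driven spread (variance averaged over the arms) = 2.14, so d = 0.516/2.144 = 0.241.
- n per arm for 80% power = 2 × (2.80/0.241)², about 271. Leaving out the episode-driven spread gives about 235; using the control-arm spread in both arms gives about 291.
- On the log rate, d = ln 2/0.8 = 0.866, so n = 2 × (2.80/0.866)² = 21 per arm.

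Grid: 20–60 s, 12–20 points deep, SD of mean saturation 1.5–2.5, SD of log rate 0.6–1.0. The mean needs about 42 to 1,730 per arm; the rate needs 12 to 33. The smallest value for the mean (42) falls at a log-rate SD of 0.6, where the rate needs 12.

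**4. Sensitivity to the log-rate SD.** The rate requires n = 2 × (2.80 × SD/ln 2)². At SD 1.5 this is about 73 per arm, and at SD 2.0 about 131. The advantage of the rate shrinks as infants differ more.

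**5. A second set of assumptions.** Take 40% fewer episodes, 2–8 per hour, 20–30 s, 12–15 points deep, SD of mean saturation 1.5–2.5, coefficient of variation of the rate 0.6–1.0, and 50–178 infants per arm. Mean saturation shifts by 0.05 to 0.40 points, with power of about 3% to 71% (correct direction only). The log rate has power of about 87% to over 99%.

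**The case against.** Four points on the other side deserve weight.

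- **The row never says mean or level.** A reader might infer that average saturations will be compared between arms. The text does not establish that. Percentage of time below a threshold is itself a continuous variable, and the sub-study section does not exclude deriving episodes from the signal. This stands: the analysis of levels is one reading of the row, not a settled fact.

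- **The article is condensed.** Episode definitions and artefact rules may sit in the full protocol or the analysis plan, neither of which is shown. Their absence alone would be no finding. But the row does not defer its method. It states one, and what it states is inconsistent and names no episode measure.

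- **The trial measures other effects of the drug.** A reader might infer that the trial could miss doxapram's claimed effect altogether. The documents do not support that. Reduced need for invasive ventilation is also a claimed effect and is covered by incidence of intubation, time to intubation and days on invasive ventilation. The hypothesis concerns death or severe disability, and the protocol sets no mediation objective from episodes to long-term outcome.

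- **The illustration has no documentary basis.** This is correct. The Discussion says that event rates fluctuate widely and are hard to detect, which could mean a larger log-rate SD and a smaller advantage for the rate. The same difficulty also argues for fixing one definition in advance.

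**Conclusion.** The point holds for the respiratory-effects analysis only. The row calls the vital signs continuous, assigns them logistic regression without a binary event, and names no episode-based measure, although fewer episodes is the stated direct effect of the drug. This rests on the text and needs no assumption.

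That levels are an insensitive substitute follows from the short duration of episodes and the use of supplemental oxygen. How insensitive cannot be derived from the documents. The contrast of about 271 with 21 per arm is an illustration, and it narrows as between-infant variation in rates grows. The number of infants with high-frequency data is not stated; only some centres contribute, so the total of 396 should not be assumed.

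The primary outcome, the trial's sample size, and the intubation and ventilation outcomes are untouched. The change is worth making because it is cheap and prevents a null result on levels from being misread.

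**What to change.** Change the respiratory-effects row of Table 1, for the centres with high-frequency data, as follows:

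- Make two measures the main ones: hypoxaemic episodes (and bradycardic episodes) per monitored hour, and percentage of monitored time below a saturation threshold. Fix the threshold before unblinding.
- Analyse the rate with a count model such as the negative binomial, or a log-rate mixed model, with monitored hours as offset and adjustment for GA and centre.
- Keep the continuous levels as description, analysed with the linear mixed model.
- Delete the sentence assigning logistic regression to all vital sign data.

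The cost is analysis code on signals already being recorded, plus one episode definition and one artefact rule agreed before unblinding. Treatment, recruitment and the primary analysis do not change. If a sample-size contrast is cited in support, label it as an illustration on assumed inputs.

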#### Randomization and blinding

Participants will be randomly allocated in a 1:1 ratio, stratified according to study centre and gestational age (<26 weeks or ≥26 weeks), and using random permutated blocks. Multiple birth infants will be randomized independently, unless parents or legal representatives explicitly request that siblings are to be allocated to the same treatment arm. Randomization and drug supply management is performed via an electronic online platform (ALEA®, FormsVision BV, Abcoude, the Netherlands).

Once the participant has been randomized, a study medication kit will be allocated. All treatment kits will be visually identical and contain either doxapram or placebo. The clinical trial centre and trial pharmacy of the Erasmus Medical Centre will manage the randomization list. The parents, researchers and medical team will have no access to the randomization list. Unblinding is only performed by an independent safety officer in emergency situations where knowledge of the study drug is considered absolutely necessary for the clinical management of the included patient.

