A limitation of this trial is that the potential direct respiratory effect of the study medication cannot be blinded, although the assessor of the primary outcome will be blinded for the allocated treatment arm. Another challenge is the absence of uniform criteria to evaluate when the frequency and duration of apnoea are considered unacceptable and an intervention is needed. Poets et al. developed an interesting apnoea score to assess the severity of apnoea, but this score is not validated yet and is mostly a reflection of current clinical practice [57]. The rate of apnoea and hypoxic events can also fluctuate largely within and between patients, and detection can be difficult [51, 58]. We therefore chose for a more pragmatic design with less strict inclusion criteria. The decisions to start doxapram in routine clinical care, to adjust its dosage, or to stop doxapram therapy are made by the attending physicians. Enrolment of a participant in the study is done according to the existing clinical protocols and can vary between centres and physicians, as does the dosing and duration of study drug therapy. This pragmatic strategy was chosen to make the trial clinically feasible, relevant and to increase generalizability to other centres. Randomization of participants is stratified per centre, and we will adjust for this stratification in the analysis. The respiratory status before starting doxapram will be evaluated in a subset of the participants using continuous monitoring data. With these data, we aim to find more objective parameters and criteria for the indication to start doxapram therapy in future patients.

This trial will provide knowledge to improve the optimal treatment of preterm infants suffering from AOP. We will evaluate the safety and efficacy of doxapram in reducing death and severe disability in the first years of life. If doxapram is safe and effective, the treatment could be implemented in more NICUs worldwide. The placebo design may also provide the opportunity to identify patients who will benefit from doxapram therapy and those who will not. Evaluation of the exposure to doxapram and keto-doxapram will enable us to optimize dosing in future individual patients. An improved, more individualized AOP treatment policy will likely prevent patients from periods of hypoxemia and unnecessary treatment risks. Overall, this randomized, placebo-controlled trial aims to improve long-term patient outcomes.

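### The vital-sign comparison names only gestational age and centre as covariates and does not say whether, or how, the infant's own pre-drug recording enters the model

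*Protocol article*

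**What the plan says.** The Respiratory effects row of Table 1 (Secondary outcomes) lists oxygen saturation, respiratory rate, heart rate and blood pressure. It makes three statements about their analysis:

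- on scale: "Vital sign data will be analysed as continuous data";
- on model and covariates: "Logistic regression analysis will be performed for all vital sign data, corrected for GA en centre";
- on repeated recordings: "Mixed model analysis will be performed to take into account repeated measurements".

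The sub-study section, Vital sign data analyses, gives source and purpose: "Some of the participating centres will collect continuous high frequency monitor data", and "The vital sign data will be used to investigate the response to doxapram therapy compared to placebo". It also aims to separate responders from non-responders. The monitor signals it names are oxygen saturation, heart rate and respiratory rate.

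The Discussion shows that pre-drug recordings exist for at least some infants: "The respiratory status before starting doxapram will be evaluated in a subset of the participants using continuous monitoring data". The purpose given there is to find objective criteria for starting doxapram, not to adjust the treatment comparison. The Discussion also says of the underlying events: "The rate of apnoea and hypoxic events can also fluctuate largely within and between patients".

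**The concern.** Response is naturally judged against the state from which the infant started. The same signal measured just before treatment is often a strong predictor of the signal on treatment, and gestational age and centre are unlikely to stand in for it. Infants will enter at different levels, since the plan describes large variation between them and leaves the entry threshold to the attending physician.

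If the pre-drug value is left out, variation between infants that could be explained stays in the error term and the confidence interval is wider than it needs to be.

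How the value enters also matters. If pre-dose recordings go into the mixed model as ordinary response rows under a single treatment effect, they dilute that effect, because no drug effect can exist before dosing. The text does not settle which approach is meant.

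**Working it through.** **The plan's own figure.** There is none to reproduce. The article gives no sample size, standard deviation, effect size or power for the vital-sign comparison.

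**Inputs from the documents.** The stated covariates are gestational age and centre. The outcome is continuous. On allocation, "Participants will be randomly allocated in a 1:1 ratio" (Randomization and blinding).

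**Inputs assumed.** The correlation rho between the pre-drug and on-treatment values that enter the model is set at 0.3, 0.5 and 0.7. For power only, the difference is set at 0.5 SD and the subset at 25, 50 or 100 infants per arm. All figures assume a linear model; they do not carry over to logistic regression.

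**Step 1: precision.** With 1:1 randomisation, adjusting for one baseline value multiplies the variance of the treatment effect by 1 − rho², and so the confidence-interval width by √(1 − rho²). The equivalent gain in sample size is 1/(1 − rho²).

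| rho | variance factor | width factor | interval narrower by | equivalent sample size |
|---|---|---|---|---|
| 0.3 | 0.91 | 0.954 | about 5% | 1.10 times |
| 0.5 | 0.75 | 0.866 | about 13% | 1.33 times |
| 0.7 | 0.51 | 0.714 | about 29% | 1.96 times |

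**Step 2: power, as illustration.** Power = Φ(d·√(n/2)/√(1 − rho²) − 1.96), with d = 0.5. For n = 50 and no adjustment: 0.5 × √25 = 2.5, and Φ(2.5 − 1.96) = 70.5%. At rho 0.5: 2.5/0.866 = 2.887, and Φ(0.927) = 82.3%.

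| infants per arm | unadjusted | rho 0.3 | rho 0.5 | rho 0.7 |
|---|---|---|---|---|
| 25 | 42% | 46% | 53% | 70% |
| 50 | 71% | 75% | 82% | 94% |
| 100 | 94% | 96% | 98% | >99% |

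**Step 3: bias or precision?** In 4000 simulated trials per correlation, with 25 infants per arm and a true difference of 0.5, the mean unadjusted estimates were 0.500, 0.497 and 0.507 at rho 0.3, 0.5 and 0.7. The mean adjusted estimates were 0.501, 0.499 and 0.502. Both methods are unbiased. The ratios of adjusted to unadjusted standard error were 0.97, 0.88 and 0.72, close to the formula.

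**Step 4: the model sentence itself.** Table 1 calls these data continuous and then prescribes logistic regression without defining a dichotomy. The section Secondary outcome analyses assigns logistic regression to dichotomous outcomes and linear regression to continuous ones. The table row conflicts with that rule and with its own preceding sentence.

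**The case against.** The strongest reply is that the mixed-model sentence lists no covariates at all. The restriction to gestational age and centre sits in the logistic-regression sentence, so a reader who infers that the plan excludes the pre-drug value from the mixed model goes beyond the text. A mixed model that includes it properly would recover much of the loss, and a condensed article may leave that to the analysis plan. This stands in part: exclusion is not shown. But the article does print a covariate list for this outcome, and adding a suitable variable to it is a concrete improvement at little cost.

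Other limits also stand:

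- **Correlation.** The Discussion describes large fluctuation within infants as well as between them. That lowers the correlation of a short pre-dose window with later values and points to the end of the range where the gain is only about 5%.
- **Availability.** Blood pressure is in Table 1 but not among the monitor signals named in the sub-study section, so a pre-drug blood pressure is not shown to exist. Nor do the documents say that the infants with pre-drug recordings are the same as those in the treatment comparison.
- **Subset size.** One might infer that the subset is small. The article says only that some centres take part and gives no number. The relative loss of precision does not depend on it.
- **Source of the variation.** One might read the Discussion as saying that infants differ because entry rests on clinical judgement. It argues the other way: fluctuation and difficult detection are given as reasons for the less strict entry criteria.

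**Conclusion.** The point holds as a matter of precision and of an unfinished model statement. Only gestational age and centre are named as covariates, and the role of the pre-drug recording is left open in a comparison meant to measure response. In a linear model, using it would narrow the interval by about 5%, 13% or 29% at correlations of 0.3, 0.5 or 0.7. The correlation is an assumption and the low end is plausible.

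A reader might infer that the omission would create or mask a drug effect through bias. The documents do not support that: allocation is randomised and stratified by centre and gestational age, so the unadjusted estimate is unbiased on average. Chance imbalance in the one trial that is run can still move its estimate, but the ordinary standard error already reflects this.

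Importance is low to moderate. This is a secondary sub-study in some centres, and neither the primary outcome nor the trial's main conclusion depends on it.

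**What to change.** In the Respiratory effects row of Table 1, or in the sub-study analysis plan:

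1. Specify a linear mixed model for oxygen saturation, heart rate and respiratory rate, and for blood pressure where a pre-drug value exists. Drop logistic regression for these continuous outcomes, unless a dichotomy is defined.
2. Include each infant's average over a fixed window before the first study dose as a covariate, beside treatment, gestational age and centre. Averaging over a window reduces the effect of short-term fluctuation on the correlation.
3. Alternatively, model the pre-dose average as a response with baseline means constrained equal between arms. This also keeps infants who have no usable pre-dose recording.
4. Fix the window and the chosen form before allocation is unblinded, so that neither is a post-hoc choice.

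The cost is one or two sentences. No new data are needed for infants whose monitoring already covers the pre-dose period. Where it does not, and possibly for blood pressure, option 3 avoids losing the infant from the analysis.
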